#### SWAT sample size

The sample size for the SWAT is limited by the host trial sample size. The SWAT opened to recruitment after the internal pilot (50 participants), therefore, approximately 428 participants (214 per group) are expected and would provide 90% power and 5% significance to detect differences in retention rates of approximately 11%.

### Screening and eligibility

#### RCT screening and eligibility

Adults presenting at trial sites (NHS hospitals) with a first-time TASD, confirmed radiologically, managed non-operatively (decided by the treating clinician and patient) will be identified as potential participants. The site team will undertake eligibility checks and details will be entered on a monthly screening log.

Participants will be excluded if they have significant neurovascular complications; bilateral dislocations; have been randomised previously; unable to adhere to trial procedures or unable attend physiotherapy within 6 weeks of injury.

All eligible participants will be provided with verbal and written information about the study. If eligible and willing to join the study, a consent form will be signed (see online supplemental material), followed by collection of baseline demographic data, preinjury and postinjury functional outcomes.

10.1136/bmjopen-2020-040623.supp1Supplementary data

#### SWAT screening and eligibility

Participants recruited into ARTISAN, who consent to being contacted by multiple methods, will be eligible for the SWAT.

### Randomisation

#### RCT randomisation

Participants will be randomised at the end of the initial advice session via a web-based system. Allocation concealment will be maintained by an independent randomisation team at WCTU, who will be responsible for generation of the sequence and will have no role in the allocation of participants. The treatment group will be allocated by computer using a minimisation algorithm with a random element and stratification by participant age (39 years old and under and 40 years old and over), hand dominance and recruiting site.

#### SWAT randomisation

Minimisation with a random factor will be used to avoid imbalance between the SWAT intervention arms. The allocation ratio will be 1:1 and stratified by the ARTISAN allocation arm. Allocation concealment will be maintained by an independent randomisation team who will be responsible for generation of the sequence and have no role in the allocation of participants.

#### Postrandomisation withdrawals

Participants may discontinue at any time without prejudice. Unless a participant explicitly withdraws consent, data will be collected until the end of the trial. For participants explicitly withdrawing consent for follow-up procedures, trial data obtained up until the point of withdrawal will be included. Participants will have the option to withdraw from the trial-related questionnaires, but continue to provide routine NHS data for trial purposes. Participants who withdraw will not be replaced. Participants may be withdrawn from the trial at the discretion of the investigator and/or trial steering committee for safety concerns.

### Interventions

#### RCT interventions

The interventions will be reported in line with the template for intervention description and replication (TIDIER) and Consensus on Exercise Reporting Template (CERT) checklists.^10 11^ All participating centres will receive an initial training session from the trial team. Following this, a lead physiotherapist at each site will be identified to complete subsequent training of additional physiotherapists. This training will be supported with web-based materials and a trial intervention manual.

All participants will receive a period of initial immobilisation in internal rotation as per UK national guidelines, for a duration of up to 2 weeks from date of injury.^1^ At this time participants will be provided with a web-link to phase 1 of the ARTISAN advice materials and provided with a paper-based booklet version covering:

What has happened to me?What can go wrong?How do I stop this happening again?How long do I have to wear my sling?Should I move my arm?How do I control my pain?When can I return to usual activities?What if something goes wrong?

All participants will subsequently receive an appointment for a physiotherapy advice session within 6 weeks of injury. At the first appointment, all participants will receive a single session of advice to aid self-management, lasting up to 1 hour and administered by an ARTISAN trained physiotherapist. Following routine assessment, the physiotherapist will deliver the above core set of intervention components and in addition:

Points of contact if complications occur or expected recovery times are not achieved.A core set of progressive phase 2 range of movement exercises and what they aim to achieve.Enhancing self-management behaviours through the addition of goal setting, exercise planning and diaries.

The physiotherapist will provide details of web-based materials, which will include all the core components above in written and video format, and will include a dedicated area for participants to set goals and keep diaries. The physiotherapist will also inform the participants that the website resources contain phase 3 progressive strengthening exercises and what they aim to achieve and later stage phase 4 progression to aid return to sports. Participants will be offered paper-based alternatives.

Following completion of the first physiotherapy appointment, the participant will be randomised, allocating them to this advice session alone or to this advice session plus the offer of additional physiotherapy.

Participants randomised to the advice session only, will only receive this physiotherapy intervention. However, if they are experiencing ongoing issues which are not improving, as part of the control intervention, the advice is for the participant to contact the clinic they attended or see their general practitione. If a participant follows this advice and self-initiates further physiotherapy, this will not be deemed a deviation from the protocol. However, if someone other than the participant initiates further physiotherapy (another clinician) then this will be deemed a protocol deviation. This data will be collected as part of the trial dataset.

Participants randomised to receive additional physiotherapy will be offered of at least one additional physiotherapy session. Each additional session will last for up to 30 min, over a maximum duration of 4 months from date of randomisation. The number and frequency of any additional sessions will be jointly agreed between the clinician and participant, in keeping with standard practice. The course of physiotherapy will involve teaching and supervising the ‘core set’ of progressive exercises offered to the control arm in addition to being able to tailor treatment as per their usual practice.

#### SWAT interventions

Participants will be randomised to receive either:

An introductory call within 2 weeks of being randomised to include thanking participants; reminding them of their valuable contribution and that they will be contacted at 6 weeks and 3, 6 and 12 months; informing them of when the trial results are expected and to contact the ARTISAN team if they have queries.A postcard-sized handwritten card, with similar content as above, signed by the chief investigator and trial manager, posted to participants within 1 week of being randomised.

#### Fidelity and quality assurance of interventions

The trial team will implement a standardised approach of evaluating fidelity^12^ of direct observations and audio recordings (twice annually); and self-reporting of the trial interventions. Any issues will be discussed by the trial management group (TMG), who will recommend appropriate action such as feedback to sites and additional training. If issues are not resolved following recommendations they will be escalated to oversight committees.

During site quality assurance visits the research teams will also be asked to provide radiological confirmation of the participants initial shoulder dislocation. If evidence is not found, participants will be withdrawn from the main trial sample, but will continue follow-up procures and retained as part of a pre-planned sensitivity analysis.

### Blinding

As the type of rehabilitation used will be clear to the participant, they cannot be blind to treatment. The treating clinician will also not be blind, but will take no part in follow-up processes, these will be managed centrally from the WCTU to reduce the assessment bias.

### Adverse event management

Serious adverse events (SAEs) will be entered onto the SAE reporting form and reported to the central study team. SAEs that may be expected will be predefined and recorded on the participant’s follow-up questionnaire. SAEs that may be expected as part of a TASD are: damage to nerve or blood vessels, fractures, redislocation, torn ligaments or muscles, persistent exacerbation of shoulder pain, restriction of range of movement, adhesive capsulitis (frozen shoulder) and persistent instability. All SAEs will be reported to the sponsor (Warwick University and University Hospitals Coventry and Warwickshire), ethics committee and oversight committees.

### End of trial

The trial will end when all participants have completed their 12-month follow-up. The trial will be stopped prematurely if mandated by the Ethics Committee; following recommendations from relevant oversight committees; or funding ceases.

### Trial oversight

The TMG will meet monthly and report to the independent trail steering committee (TSC) and data monitoring and safety committee (DMSC). The TSC and DMSC will hold meetings annually and be responsible for approval of the protocol, monitoring and supervising progress.

### Patient and public involvement

The clinical team consulted with patients when developing this project and subsequently we had a meeting with a group representing our target participants. We discussed experiences and expectations of services and plans for the trial. Service users’ perspectives were key in the development of this protocol. Patient and public involvement (PPI) membership is represented on TMG and TSC committees and have reviewed all study materials. PPI members of the team will contribute to dissemination on trial completion.

### Analysis

#### RCT statistical analysis

The internal pilot will inform and test recruitment strategies for the main trial in 12 sites over 6 months. A recruitment rate of one participant per month per centre was estimated for the 6 months pilot phase, with 50 participants in total. The decision to progress to the main trial will be made based on predefined progression criteria. The criteria for continuing will be achievement of 75%–100% of the recruitment target; criteria for the need to review and amend trial procedures before continuing will be achieving 50%–75% of the target; criteria for not proceeding will be achieving less than 50% of the target. These randomised participants will be retained in the final analysis.

A detailed statistical analysis plan which will be agreed with the DMSC prior to the analyses taking place. All data will be reported in accordance with the Consolidated Standards of Reporting Trials (CONSORT) statement. Baseline data will be summarised to check comparability between treatment arms, and screening data will be checked to highlight any characteristic differences between those individuals in the study, those ineligible and those eligible but withholding consent.

The research team recognise the theoretical possibility of therapist effects. Here, we are randomising by individual; it is the same therapist who will be seeing people in both arms of the trial, and the treatment is individually delivered ensuring there are no group effects. To keep presentation of key information as standard throughout the study, the initial therapist contact will be described in the study manual and will use supporting media. We intend to recruit from a minimum of 30 sites where there will be multiple therapists taking part over the course of the study (eg, sickness and holiday coverage). This gives the number of estimated therapist level clusters upwards of 60 and potential cluster sizes of around four participants in each arm of the trial. With such small cluster sizes, even if there were to be important therapist effects, their effect on statistical power would be minimal.

To address the possibility that these might exist, a single interim analysis is preplanned to re-estimate the sample size. This will occur after approximately 200 participants have completed the 3 months follow-up questionnaire, while recruitment is still open. The pooled SD of the primary outcome and presence of therapist effects will be estimated by calculating the therapist intraclass correlation coefficient and its 95% CI. Models will not include treatment effects. A revised sample size calculation will be discussed with DMC and TSC and if appropriate, permission requested from the funder to adjust the sample size.

All primary analyses are planned to be on an intention-to-treat basis with secondary per protocol analyses. The main analysis will investigate differences in the primary outcome measure, 6 months after randomisation, between the two treatment groups. Unadjusted and adjusted regression analyses will be used to estimate the between group difference. The adjusted analyses will adjust for the stratification variables, baseline scores and any other clinically important variables. Since individual clinicians will treat only a small number of participants enrolled in the trial, we do not expect clinician-specific effects to be important in this study.

Descriptive statistics of functional outcome data (ie, QuickDash and EQ-5D-5L) at each time point will be constructed with between group analyses following the method set out for the primary analysis above. Patterns of recovery will also be explored. Secondary analyses will includeχ^2^ tests to compare the number of dislocations and other complications between allocation groups. For important complications (eg, dislocations), Kaplan-Meier curves of the time to complication will be constructed. If sufficiently large numbers of complication groups are observed, Cox regression models will be constructed to compare the time to complication in each arm. Temporal effects will be investigated using a multilevel model of all follow-up data.

Two prespecified subgroup analyses will be undertaken to assess whether there is evidence of differing intervention effect: hand dominance (injured shoulder dominant arm vs injured shoulder is non-dominant arm and age (younger participants vs older participants). Because of the small sample size these analyses will be exploratory. The subgroup analyses will follow the methods described for the primary analysis, with additional interaction terms incorporated into the mixed-effects regression model to assess the level of support for these hypotheses. We will additionally present the main result separately for younger and older age groups for the benefit of future systematic reviewers who may be focused on different age groups. We will draw no inference from these analyses.

Careful monitoring of missingness and crossovers will be conducted. If judged appropriate, multiple imputation will be used to account for missing data, with all necessary assumptions reported. If large numbers of treatment crossovers are observed, Complier-Average Causal Effect models will be used.

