### Sample size

#### RCT sample size

A worthwhile difference from this intervention is four points on the OSIS.^8 9^ The SD of the OSIS 6 months after injury is 10 points.^8 9^ However, the literature has predominantly included a young population, given that we will recruit a wider range of ages a larger SD is expected, therefore an SD of 12 is more likely. To show a four-point difference at 5% significance level with 90% power allowing a margin of 20% loss during the follow-up needs a minimum of 478 participants.^5 9^

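### The reason given for setting therapist effects aside does not cover the sessions being tested, so the primary 95% CI may be slightly too narrow if therapists in the physiotherapy arm differ

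*Protocol article*

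**What the plan says.** Under RCT statistical analysis, the protocol article accepts that therapist effects are possible in theory. It then gives reasons to discount them: randomisation is by individual, the same therapist sees people in both arms, and treatment is delivered one to one. With at least 60 therapists and about four participants per therapist in each arm, it concludes: "With such small cluster sizes, even if there were to be important therapist effects, their effect on statistical power would be minimal".

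The same section plans one interim look to estimate the pooled SD and the therapist ICC, in models without a treatment term, in order to re-estimate the sample size. The main analysis is then unadjusted and adjusted regression. The listed covariates are the stratification variables (age group, hand dominance, site), baseline scores and other clinically important variables. On clinicians it says only that "we do not expect clinician-specific effects to be important in this study". The subgroup analyses are to follow the primary methods, with "additional interaction terms incorporated into the mixed-effects regression model".

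RCT randomisation places randomisation at the end of the initial advice session. RCT interventions describes what follows: "Participants randomised to the advice session only, will only receive this physiotherapy intervention", whereas the other arm is offered further sessions over up to 4 months, in which physiotherapists teach the core exercises "in addition to being able to tailor treatment as per their usual practice". Advice-arm participants who are not improving may seek physiotherapy themselves, and this is not a deviation.

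**The concern.** A therapist who sees both arms shifts both means alike, and that shift cancels from the contrast. This holds for the advice session. It does not hold for the additional sessions, which are the randomised component, are open to tailoring, and are planned in one arm only. After randomisation the design is partially nested: participants in the physiotherapy arm share therapists, while most advice-arm participants have no further planned contact.

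If some therapists obtain better results than others, outcomes within a therapist's physiotherapy caseload are correlated. Ordinary regression counts the therapist variance within the total residual variance but treats those participants as independent. The standard error of the primary Oxford Shoulder Instability Score (OSIS) difference is then too small. At stake are the coverage of the 95% CI, the true size of the 5% test and a small part of the stated power.

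The plan is also uneven. It regards the therapist ICC as important enough to reopen the sample size, yet gives it no stated role in the final model.

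**Working it through.** **Inputs.** From RCT sample size: "four-point difference at 5% significance level with 90% power", a 4-point target, SD 12, 20% loss, 478 participants. From RCT statistical analysis: 60 or more therapists, about four participants each per arm. Assumed: a two-sided test, and an ICC of 0.02 to 0.10, because the article gives none.

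**Step 1: reproduce 478.** The normal formula gives 2 × [12 × (1.960 + 1.282)/4]² = 189.1, so 190 per arm and 380/0.8 = 475 in total. The t-based calculation gives 190.1, so 191 per arm; 191/0.8 = 238.75, rounded up to 239, and 2 × 239 = 478. The figure is reproduced exactly and contains no therapist design effect.

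**Step 2: cluster size.** Randomised: 239/60 = 3.98 per therapist in the physiotherapy arm, which agrees with the article's figure of about four. Analysed: 478 × 0.8/2 = 191.2 per arm, and 191.2/60 = 3.2 per therapist.

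**Step 3: effect on the contrast.** With clustering in one arm only, the design effect in that arm is DE = 1 + (m − 1) × ICC, and the ratio of true to ordinary standard error is r = √[(1 + DE)/2]. The actual type I error of a nominal 5% test is 2 × [1 − Φ(1.960/r)]. The ordinary standard error is 12 × √(2/191.2) = 1.227, which gives a 95% CI half-width of 2.41 points and power of 90.3%. The power column below is Φ(4/(1.227 × r) − 1.960), that is, for a test that uses the correct standard error.

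| m | ICC | DE | r | Type I error | Power | CI half-width |
|---|---|---|---|---|---|---|
| 3.2 | 0.02 | 1.044 | 1.011 | 5.25% | 89.7% | 2.43 |
| 3.2 | 0.05 | 1.110 | 1.027 | 5.64% | 88.7% | 2.47 |
| 3.2 | 0.10 | 1.220 | 1.054 | 6.28% | 87.1% | 2.53 |
| 4 | 0.02 | 1.060 | 1.015 | 5.35% | 89.5% | 2.44 |
| 4 | 0.05 | 1.150 | 1.037 | 5.87% | 88.2% | 2.49 |
| 4 | 0.10 | 1.300 | 1.072 | 6.76% | 86.0% | 2.58 |

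**Step 4: check by simulation.** The simulation used ordinary regression with 191 per arm, 30 sites as fixed effects, a therapist effect in the physiotherapy arm only and 8,000 replicates (simulation error about 0.24 percentage points, from √(0.05 × 0.95/8000)). Type I error was:

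- 60 therapists, equal caseloads: 5.3% at ICC 0, then 5.7%, 6.0% and 6.6% at ICC 0.02, 0.05 and 0.10.
- 60 therapists, caseload coefficient of variation 0.7: 6.6% at ICC 0.05 and 8.2% at 0.10.
- 30 therapists, equal caseloads: 6.8% at ICC 0.05 and 9.0% at 0.10.
- Therapist effect identical in both arms, 60 therapists: 5.1% at ICC 0.05 and 4.8% at 0.10.

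Adjusting for site therefore does not remove the excess. The last line shows that the article's argument is sound for the shared session and fails only for effects confined to one arm. The uneven caseloads and the 30 therapists are assumptions; the article expects 60 or more.

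**The case against.** Four objections have weight.

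- **Small clusters limit the standard-error problem as well as the power loss.** This stands. The same (m − 1) × ICC term drives both, and at the plan's caseload the true standard error exceeds the ordinary one by only 1% to 5%. The larger type I errors need uneven caseloads or fewer therapists than the article expects. Sickness and holiday cover, which the article mentions, makes uneven caseloads plausible but does not establish them.
- **Random-effect structure is normally left to the SAP, which is not shown.** This stands in part. A reader might infer that the primary model certainly has no therapist term. The article does not support that: the subgroup text implies a random effect somewhere in the primary approach and does not name it. What remains is a stated rationale that does not fit the randomised component, and two descriptions of the model that do not match. An SAP that follows this text would inherit both.
- **The advice arm is not free of therapists.** This stands. A reader might infer that only one arm is treated by therapists, but both arms have the advice session and advice-arm participants may start physiotherapy themselves. The accurate statement is that further sessions are planned in one arm only.
- **The interim look deals with power.** This stands in part. Re-estimation could restore lost power, and the planned baseline adjustment, for which 478 takes no credit, could offset a loss of one to three points. Neither corrects the final standard error.

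**Conclusion.** The point holds in a conditional and modest form. The same-therapist argument covers only the contact before randomisation, so it cannot justify setting aside clustering in the sessions under test. If the physiotherapy-arm ICC is above zero and the analysis ignores it, the 95% CI for the OSIS difference is slightly too narrow.

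At the plan's caseload this is close to negligible at ICC 0.02 and small at 0.05 to 0.10. It becomes material, with type I error about 7% to 9%, only when an ICC in that upper range meets uneven caseloads or fewer therapists. Power falls to between about 89.7% and 87.1% before any gain from baseline adjustment.

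It would go too far to say that the planned interval is wrong as it stands. That would need a positive ICC, which the article does not report, and a final model known to omit the therapist. The correction is worth making because it is cheap and, in simulation, modelling the clustering in the physiotherapy arm returned type I error to about 5%.

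**What to change.** In the main-analysis text under RCT statistical analysis, and in the SAP, specify that the adjusted primary model includes a therapist random effect in the physiotherapy arm only, with arm-specific residual variances and a small-sample degrees-of-freedom correction. At minimum, make this a named sensitivity analysis reported beside the primary result.

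Three details need settling in advance:

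- **Cluster rule.** Therapists may change during a course, and some participants may attend no additional session. One workable rule assigns each participant to the therapist who delivers most of their additional sessions and treats participants who attend none as their own cluster. Everyone then stays in the intention-to-treat analysis.
- **Data capture.** Confirm that the identity of this therapist is recorded. The interim ICC needs some therapist identifier, but the article does not say whether it is the advice or the treating therapist.
- **Consistency.** Name the same random effect in the subgroup text.

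Limit the same-therapist sentence to the advice session, and make the statement on power conditional on the ICC, with a range such as the one above.

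The cost is wording plus the check on data capture. The analysis pays with a slightly wider interval when therapist variation is present and, with about three analysed participants per therapist, an imprecise variance estimate that may be zero. In that case the result will be close to the planned regression but not identical, because of the separate residual variances and the degrees-of-freedom correction.

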### RCT secondary objectives

To estimate comparative cost-effectiveness (cost/quality-adjusted life-years, QALY) of the two trial treatments, from an National Health Service (NHS) and personal social services perspective.To determine the difference in complication rate (eg, shoulder redislocation) in the first 12 months between the trial treatment groups.To quantify and draw inferences between the functional status (OSIS) of the trial treatment groups at 6 weeks, 3 and 12 months.To quantify and draw inferences on observed differences in the functional status (Disabilities of the Arm, Shoulder and Hand) of between the trial treatment groups at 6 weeks, 3, 6 and 12 months.To quantify and draw inferences on observed differences of health-related quality of life (EQ-5D-5L) between the trial treatment groups at 6 weeks, 3, 6 and 12 months.To qualitatively explore participants’ experiences of receiving the trial treatments and identify facilitators and obstacles to adhering to them.

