#### SWAT analysis

All eligible participants will be included on an intention-to-treat basis, using two-sided statistical significance at the 5% level. We will summarise baseline characteristics of participants by the type of SWAT intervention sent. An average cost per participant will be estimated for each SWAT intervention arm. For the primary outcomes of questionnaire response rates, the difference in proportions will be calculated with 95% CIs, and the primary analysis will be a χ^2^ test to assess statistical association. Additionally, a logistic regression adjusting for age, gender and host trial treatment allocation will be performed to investigate the effects of these variables. A per-protocol analysis will also be performed.

The secondary outcome of time to questionnaire return will be assessed by a Kaplan-Meier curve and the SWAT interventions compared by log rank test. Cox regression will be applied adjusting for participant age, gender and host trial treatment allocation, and the effect of the intervention reported. The requirement for any questionnaire return reminder will be analysed in the same way as the primary outcome).

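### Redislocation and other complications get only an unadjusted chi-square as their unconditional test, although allocation is minimised on age, hand dominance and site; if redislocation depends strongly on age, some power is lost

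*Protocol article*

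**What the plan says.** **Allocation.** RCT randomisation describes minimisation with a random element and "stratification by participant age (39 years old and under and 40 years old and over), hand dominance and recruiting site".

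**Objective.** One of the RCT secondary objectives is "To determine the difference in complication rate (eg, shoulder redislocation) in the first 12 months between the trial treatment groups".

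**Functional outcomes.** RCT statistical analysis gives OSIS unadjusted and adjusted regressions. The adjusted one includes the stratification variables and baseline scores. QuickDASH and EQ-5D-5L follow the same method.

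**Complications.** The same section gives these a different method: χ² "tests to compare the number of dislocations and other complications between allocation groups". For important complications, "Kaplan-Meier curves of the time to complication will be constructed". A model comes only on a condition: "If sufficiently large numbers of complication groups are observed, Cox regression models will be constructed to compare the time to complication in each arm". No covariates are named for the test or the model. The section also says that a detailed statistical analysis plan will follow. It is not among the documents at hand.

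**The concern.** A chi-square test judges the difference between arms against the pooled binomial variance, as if allocation had been simple randomisation. Minimisation removes most of the chance imbalance in age. If age predicts redislocation, the arm difference then varies less than the test assumes, so the p-value tends to be too large and power is lost.

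Kaplan-Meier curves are descriptive and the Cox model may never be fitted, so the chi-square is the one formal comparison certain to be made. It bears on a named secondary objective, and the Introduction links redislocation to ongoing morbidity. The sample size was set for OSIS alone, so power for redislocation was never secured and avoidable loss is worth removing. The error would lean towards reporting no evidence of a difference in a harm.

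**Working it through.** **1. The plan's own figure.** Inputs from RCT sample size: difference 4, SD 12, 5% (taken as two-sided), 90% power, 20% loss.
- Normal approximation: n per arm = 2 × (1.960 + 1.282)² × 12² / 4² = 189.1, so 190; total 380; 380 / 0.8 = 475.
- t-based: 190.1, so 191 per arm; total 382; 382 / 0.8 = 477.5, so 478.

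The stated 478 reproduces, with about 382 analysed. The article gives no event rate, effect size or power for redislocation.

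**2. Formula.** Let f be the share aged 39 and under, py and po the redislocation risks in the younger and older groups, and P = f·py + (1 − f)·po. With age balanced between arms, the ratio of the true variance to the one the chi-square uses is

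r = [f·py(1 − py) + (1 − f)·po(1 − po)] / [P(1 − P)],

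and the true size of a nominal 5% test is about 2 × [1 − Φ(1.96 / √r)].

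Worked cases with f = 0.5 (f and the rates are assumptions):
- 30% v 5%: P = 0.175; r = (0.105 + 0.02375) / 0.144375 = 0.892; 1.96 / √0.892 = 2.075; size 3.8%.
- 50% v 5%: P = 0.275; r = (0.125 + 0.02375) / 0.199375 = 0.746; 1.96 / √0.746 = 2.269; size 2.3%.
- 20% v 10%: P = 0.15; r = (0.08 + 0.045) / 0.1275 = 0.980; size 4.8%.

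**3. Simulation.** Power is for a common odds ratio of 0.5, two-sided 5%.
- A: 191 per arm, exact age balance, 100,000 trials; chi-square v Mantel-Haenszel over two age strata.
- B: 478 randomised by minimisation on age, dominance and 30 sites (preferred arm with assumed probability 0.8), 80% followed up, 3,000 trials; chi-square v Mantel-Haenszel over age × dominance.

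| Assumed rates, younger v older | r | Size by formula | A: chi-square size | A: power, chi-square v stratified | B: size, chi-square v stratified | B: power, chi-square v stratified |
|---|---|---|---|---|---|---|
| 10% v 10% | 1.000 | 5.0% | – | – | 4.6% v 4.6% | 42.2% v 41.7% |
| 15% v 10% | 0.994 | 4.9% | 5.0% | 49.4% v 49.2% | – | – |
| 20% v 10% | 0.980 | 4.8% | – | – | 5.2% v 5.4% | 54.4% v 54.5% |
| 20% v 5% | 0.949 | 4.4% | 4.4% | 46.9% v 48.4% | – | – |
| 30% v 5% | 0.892 | 3.8% | 3.9% | 55.9% v 59.4% | 4.1% v 4.9% | 56.5% v 59.5% |
| 40% v 5% | 0.824 | 3.1% | 3.2% | 61.3% v 67.0% | – | – |
| 50% v 5% | 0.746 | 2.3% | 2.3% | 62.8% v 70.9% | 2.9% v 5.5% | 61.2% v 70.1% |

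The Monte Carlo standard error of a 5% size in B is √(0.05 × 0.95 / 3000) = 0.4 points, so 5.2% in the 20% v 10% row is compatible with the 4.8% from the formula.

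**4. Sensitivity.** With full follow-up in B, power is 65.6% v 69.0% at 30% v 5%, and 72.6% v 79.2% at 50% v 5%. With f between 0.4 and 0.6, the size by formula is 3.7% to 4.0% and 2.1% to 2.6% respectively. The pattern does not depend on exact balance, full follow-up or an even age split.

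**The case against.** **The size is not in the document.** No redislocation rate is given, overall or by age. The Introduction says who sustains the injury, not who redislocates. A reader might infer that power is lost wherever redislocation depends on age. The table does not support that: the loss is nil at 15% v 10% and at 20% v 10%, and about 1.5 points at 20% v 5%. It passes 5 points only at about 40% v 5% or steeper. This objection stands and limits the point to strong age gradients.

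**The chi-square is not the whole plan.** The wording is open-ended, and Cox regression follows if numbers allow. The steep-gradient scenarios are also the event-rich ones: 40% v 5% implies about 0.225 × 382 = 86 events under the null, where the Cox condition is more likely to be met. That is fair, but the condition has no threshold and the chi-square remains the only comparison certain to be made.

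**The Cox covariates.** A reader might take their absence, beside the companion retention study's (SWAT's) "Cox regression will be applied adjusting for participant age, gender and host trial treatment allocation", as a decision not to adjust. It is not. Covariates are commonly left to the analysis plan, and the SWAT also puts a chi-square first and adds adjusted regression.

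**Other inferences that fail.** Nothing shows a cost from ignoring hand dominance in itself. Nor can one say that a confidence interval would be too wide, because none is specified for complications.

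**Limited consequence.** In scenarios A and B, both at about 382 analysed, power at an odds ratio of 0.5 stays below 80% under either test, so the number of events matters more than the choice of test. This stands, and it sets the priority.

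**Conclusion.** The point holds as a modest inefficiency in a stated method, not as a demonstrated error. The chi-square ignores factors that the design balances and that the functional-outcome analyses use. It is conservative if age is strongly prognostic for redislocation.

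Under assumed rates, with half of participants aged 39 and under and about 382 analysed, the loss at an odds ratio of 0.5 is 3 to 4 power points at 30% v 5% and 8 to 9 points at 50% v 5%. It is negligible at modest gradients. The article treats age as important (minimisation factor, prespecified subgroup, separate results by age group), which makes an age effect plausible but fixes no rate.

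False positives are not increased, and the primary OSIS analysis is untouched. Low priority.

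**What to change.** Under RCT statistical analysis:
- Make the main comparison of redislocation one of participants with at least one event, either by a Mantel-Haenszel analysis (test and risk difference) stratified by age group and hand dominance, or by a logistic model with arm, age and hand dominance. Hand dominance is included because it was used in allocation, not because a loss from omitting it has been shown.
- Use the same covariates if the Cox model is fitted.
- Keep the chi-square as a supporting result, and a plain or exact test for complications too rare to adjust.
- Leave site out of the binary analysis, because 30 or more levels are too sparse.

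**Cost.** A few lines of wording and one model. Age and hand dominance are already recorded for randomisation, so no new data or participants are needed. In the scenarios without a marked age gradient, stratifying cost essentially no power. A logistic model gives an odds ratio conditional on the covariates; the stratified risk difference stays closer to the stated objective.
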